## Abstract

Children with Juvenile Idiopathic Arthritis (JIA) are at a currently unpredictable risk of a blinding, often asymptomatic, co-existent eye disorder, anterior uveitis which requires prompt treatment. The unpredictability of this insidious disorder commits children with JIA to three-monthly expert clinical examinations in specialist eye centres often located far from their homes. Optical coherence tomography of the ocular anterior segment (AS-OCT) has been shown to be an acceptable, repeatable and sensitive modality for uveitis detection, but is not standard care. This feasibility randomised controlled trial (RCT) aims to inform a future full-scale RCT comparing current routine practice (expert slit lamp examination, SLE) to AS-OCT for the surveillance of uveitis in children at risk. Eighty children aged between 2 and 12 years old and diagnosed with JIA within the preceding year will be included. Participants with an existing diagnosis of uveitis, other ocular co-morbidities or those unable to complete examinations or provide informed assent will be excluded. Participants will be randomised to SLE (control) or AS-OCT (intervention) examination at a frequency consistent with the current national programme for childhood uveitis surveillance. Children in the intervention arm will also have standard examination at 6 and 12 months after study entrance. Outcomes of interest will be feasibility (recruitment and attrition rates), clinical metrics (proportion diagnosed with uveitis or other ocular disorders at 12 months after study entrance), quality of life outcomes (PedsQL), and resource use. Additionally, comparative analysis of AS-OCT versus SLE (‘gold standard’ reference testing) findings at 6 and 12 months for those in the intervention arm will provide the proof-of-concept data necessary to develop and undertake a larger scale trial. Trial registration: This trial has been registered with clinicaltrails.gov (NCT05984758).

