### Sample size

As a feasibility study, there is no formal power calculation based on clinical non-inferiority for a diagnostic intervention [17]. To ‘quantify’ and assess the concept that imaging-based surveillance is not inferior to clinical slit-lamp examination in the detection of active anterior uveitis in children at risk, the starting point will be that that SLE findings (assumed to be abnormal in 100% of children with an active anterior uveitis) and AS-OCT findings will concord in at least 95%.

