### Randomisation and allocation

Coordinated registration and allocation of participant trial numbers will be used. Participants will be allocated using computer-generated permuted block randomisation into one of two arms (1:1, block size = 4) stratified by age (8 and under, over 8). This will be undertaken centrally by the coordinating trial team using Sealed envelope (www.sealedenvelope.com). Allocation will not be concealed, and participants cannot be masked to their allocation to routine (slit lamp examination) or imaging-based surveillance (AS-OCT) examinations.

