### Data collection and processing

Data will be entered into electronic data collection forms (DCFs) using the REDCap platform, with collection undertaken during study visits by research associates or clinicians and reviewed for completeness by an investigator. Alongside the data collection forms, optical coherence tomography (OCT) images will be collected from participants.

To limit data missingness, the following approaches will be used

- Validation rules within the REDCap form (i.e., form submission will not be permitted if data entry points have not been completed)

- Incoming data review monthly by the study team and screening committee to identify missingness, and any patterns of/ reasons for missingness within the study dataset

- Exclusion from outcomes analysis of participants lacking a full dataset for more than two consecutive study visits

Patient data will not be transferred to any party not identified in this protocol and will not to be processed and/or transferred other than in accordance with the patients’ (parent’s) consent. Direct access to the data will be granted to authorised representatives from the Sponsor, host institution and the regulatory authorities to permit study-related monitoring, audits and inspections. This trial will collect personal data (e.g., participant names), including special category personal data (e.g., participant medical information) and this will be handled in accordance with all applicable data protection legislation. Data (including special category) will only be collected, used and stored if necessary for the trial. The database and randomisation system will be designed to protect patient information in line with the GDPR. All documents will be stored securely and only accessible by study staff and authorised personnel.

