### Analysis

Proportions will be reported as point estimates with 95% confidence intervals. Levels of missing data will be explored with respect to certain baseline characteristics, e.g., age and measures of disease severity to assess biases. All harms or unintended effects in each group will be reported. Initial trial success will be defined as: recruitment rates of > 4 recruits/month, or generation of information on barriers to recruitment; adverse event (incidence of new sight threatening complications in imaging-based surveillance group) rate of 0; adherence to surveillance programme of > 75% or understanding of barriers to adherence. We will seek to identify potential cost drivers to inform the collection of the data for cost-effectiveness analyses within a future definitive study. Within this feasibility trial, effect sizes (of ‘discrimination’ of disease) and variability in outcomes will be estimated with 95% confidence intervals to inform the sample size calculations for a full-scale trial. Efficacy and safety will be analysed according to randomisation group set, which will include all patients who underwent randomisation and who had recorded outcomes (positive detection) during the first 12 months or who completed at least 12 months of surveillance examinations. Missing outcomes (due to attrition) will be considered as an adverse outcome. We will compare the two study arms groups using two-by-two chi-square tests for equality of proportions for disease detection/ adverse outcomes within the OCT arm as compared with the ‘gold standard’ slit lamp examination group.

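### The analysis set leaves out undetected children who drop out, the next sentence counts them as adverse outcomes, and a third rule cuts differently, so the between-arm result depends on which rule is followed

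*Protocol article*

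**What the plan says.** Three statements decide who is analysed and how a dropout counts.

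- **Analysis set (Analysis).** "Efficacy and safety will be analysed according to randomisation group set", a set made up of randomised children "who had recorded outcomes (positive detection) during the first 12 months or who completed at least 12 months of surveillance examinations".
- **Missing outcomes (Analysis, next sentence).** "Missing outcomes (due to attrition) will be considered as an adverse outcome".
- **Visit-based exclusion (Data collection and processing).** Listed among the measures to limit missing data: "Exclusion from outcomes analysis of participants lacking a full dataset for more than two consecutive study visits".

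The counts feed "two-by-two chi-square tests for equality of proportions for disease detection/ adverse outcomes within the OCT arm", compared with the slit lamp arm. The Analysis section also says that estimates from this trial will inform the sample size of the full-scale trial. None of the three statements refers to another.

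**The concern.** The analysis set keeps a child without 12 months of follow-up only if uveitis was detected. An undetected child who leaves at month 5 is out; a child detected at month 5 is in. That selects on the outcome after randomisation and pushes the detection proportion up.

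The missing-outcome sentence then gives a value to the children whom the set has just removed. Either they are in the denominator and count as adverse, or they are not in it. The visit-based exclusion draws the line in another place again.

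The meaning of an adverse outcome adds to the difficulty. Study outcome measures lists new anterior chamber inflammation as the first kind of adverse event, so detecting uveitis is both the aim of surveillance and a recorded adverse event. The plan does not say whether a dropout is to be coded as detected uveitis, missed uveitis or a complication.

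At stake are the between-arm comparison and the proportions handed to the definitive trial. Allocation is not masked, so dropout could differ between arms, and the choice between rules could be made after the data are seen.

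**Working it through.** **Inputs from the protocol.** "Eighty children aged between 2 and 12 years old" (Abstract) and "one of two arms (1:1, block size = 4" (Randomisation and allocation) give 80 / 2 = 40 per arm. Sample size says "there is no formal power calculation based on clinical non-inferiority for a diagnostic intervention". No event or attrition rate is stated, so there is no figure of the plan's own to reproduce.

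**Assumptions.** Attrition of 5% to 25%; 0, 2 or 4 observed events per arm.

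**Step 1. How each rule treats the same child.**

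| Child | Analysis set | Missing-outcome sentence | Visit-based exclusion |
|---|---|---|---|
| Undetected, misses only the last one or two visits | out | in, adverse | in |
| Undetected, leaves early and misses three or more visits in a row | out | in, adverse | out |
| Detected after three or more incomplete visits in a row | in | not affected | out |

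**Step 2. Rate in one arm.** Let n = 40, e = observed events and m = dropouts without an outcome. Excluding dropouts gives e/(n − m). Counting missing as adverse gives (e + m)/n. With e = 2:

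| Attrition | m | Dropouts excluded | Missing = adverse |
|---|---|---|---|
| 5% | 2 | 2/38 = 5.3% | 4/40 = 10% |
| 10% | 4 | 2/36 = 5.6% | 6/40 = 15% |
| 20% | 8 | 2/32 = 6.3% | 10/40 = 25% |
| 25% | 10 | 2/30 = 6.7% | 12/40 = 30% |

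Over the same attrition range, e = 0 gives 0% against 5% to 25%, and e = 4 gives 10.5% to 13.3% against 15% to 35%.

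**Step 3. All three rules on one data set.** Take e = 2 and 8 dropouts, of whom 5 miss more than two consecutive visits.

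- Analysis set: 2/32 = 6.3%.
- Visit-based exclusion, then missing = adverse: (2 + 3)/(40 − 5) = 5/35 = 14.3%.
- Missing = adverse in all randomised: 10/40 = 25.0%.

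**Step 4. The planned test.** Uncorrected Pearson chi-square, N(ad − bc)² divided by the product of the four margins, with 2 events per arm and 10 versus 2 dropouts.

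- Missing = adverse, 12/40 versus 4/40: 80 × (12×36 − 28×4)² / (16×64×40×40) = 5.0, p = 0.025.
- Dropouts excluded, 2/30 versus 2/38: 68 × (2×36 − 28×2)² / (4×64×30×38) = 0.060, p = 0.81.

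Smaller imbalances do not cross 0.05. With 8 versus 4 dropouts p is 0.264 or 0.903; with 10 versus 4 it is 0.108 or 0.851.

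**Step 5. Bias from the analysis set alone.** Assume a true 12-month uveitis risk r = 0.15 and dropout d spread evenly over the year, so that on average half of the dropouts' events are seen.

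- Observed positives: r(1 − d/2). At d = 0.20 this is 0.15 × 0.90 = 0.135.
- Event-free completers: (1 − r)(1 − d) = 0.85 × 0.80 = 0.68.
- Analysis set reports 0.135 / (0.135 + 0.68) = 16.6%, against a true 15%.
- Missing = adverse in all randomised: the undetected dropouts are 0.20 − 0.015 = 0.185, so 0.135 + 0.185 = 32%.

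At d = 0.05 the analysis set gives 0.14625/0.95375 = 15.3%; at d = 0.25 it gives 0.13125/0.76875 = 17.1%.

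**The case against.** Several counter-arguments have weight.

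- **The two exclusions are compatible.** The analysis set and the visit-based rule can be applied together, and a child with three incomplete visits in a row would often fail the 12-month condition as well. This stands. The direct contradiction is between the missing-outcome sentence and the exclusions. The visit-based rule is a further inconsistent cut.
- **The positive-detection limb has a purpose.** A uveitis diagnosis ends participation, so detected children cannot complete 12 months and must be kept somehow. True, but keeping them while dropping undetected early leavers is what makes membership depend on the outcome.
- **The gap partly reflects a change of quantity.** Comparing 16.6% with 32% sets a detection proportion beside a composite of detection and missingness. This is fair, and it is the difficulty: the plan does not say which quantity it means.
- **This is an unpowered feasibility trial, and attrition is already a separate main outcome.** Both are true. They limit the reach of the point but do not remove the conflict, which is stated in the text and not left to an unseen analysis plan.

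A reader might go further and infer that dropout alone would turn the safety progression light red. The documents do not support this. Study outcome measures and Analysis both define that criterion as sight-threatening complications in the imaging arm, and neither says that a dropout is one. On that wording dropouts add no cases. Because the missing-outcome sentence closely follows the one on efficacy and safety, and its key term is undefined, it is still worth excluding this reading in the text.

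A reader might also infer that the visit-based exclusion inflates adherence. It removes children only from the outcomes analysis and says nothing of the adherence denominator. A child can also attend and still lack a full dataset.

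**Conclusion.** The contradiction holds and should be resolved before any outcome data are examined. As written, the between-arm comparison is indeterminate. At 40 per arm with 2 observed events and 5% to 25% attrition, the same data yield 5.3% to 6.7% or 10% to 30%, and a marked imbalance in dropout (10 versus 2) moves the test from p = 0.81 to p = 0.025. These figures rest on assumed rates, and the test crosses 0.05 only when dropout is clearly unequal.

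The outcome-dependent set causes only a modest bias by itself: 16.6% against 15% at 20% dropout, which is 1.6 percentage points or less than one child in 40 (0.016 × 40 = 0.64). The main problem is that incompatible rules stand side by side without precedence.

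The effect is confined to the comparison of detection and harms and to the estimates passed to the full-scale trial. The recruitment and attrition metrics are not affected, and no progression light is shown to change.

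**What to change.** 1. For the between-arm comparison of uveitis detection and harms, analyse all randomised children in their allocated arm. Delete the positive-detection or completion condition in Analysis and the visit-based exclusion in Data collection and processing.
2. Name one primary missing-outcome rule that uses observed follow-up. Cumulative incidence of detection, censored at the last examination, is one suitable choice; state its assumption that dropout is non-informative.
3. Keep missing = worst case only as a labelled sensitivity analysis, paired with a best case.
4. Define adverse outcome, and keep detection of uveitis apart from harm.
5. Analyse agreement between AS-OCT and slit lamp examination in intervention-arm children with paired examinations. The all-randomised rule cannot apply there, because this outcome exists in one arm only.
6. State that the safety criterion counts only observed sight-threatening complications, with attrition reported separately as Study outcome measures already plans.

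The cost is rewording in two sections and a little extra analysis. No additional participants, visits or data collection are needed.

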**Fig 1 pone.0316410.g001:**
[figure not shown]
SPIRIT schedule of assessments. ^a^ Visits for those within 6 months of diagnosis: newly diagnosed: Day 1, Week 8, Week 16, Week 28, Week 40, last visit Week 52.Visits for those entering study outside the 6-month widow: Day 1, Week 13, Week 26, Week 39, Week 52.^b^ Concomitant use of a. immunosuppression or immunomodulation (and dose); any eye or visual symptoms since last visit; any other parental concerns.^c^ Measured with age-appropriate method: Cardiff cards, Thomson Kays or Thomson LogMAR in each eye separately.^d^ Heidelberg Spectralis OCT2 and Optovue RTVue anterior segment cube and single line scans.^e^ A diagnosis of new onset uveitis at any visit results in exit from the trial.

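### The between-arm chi-square ignores the age strata used in randomisation: a minor mismatch with a one-sentence remedy

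*Protocol article*

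**What the plan says.** Under Randomisation and allocation, the allocation is "1:1, block size = 4) stratified by age (8 and under, over 8"). Age is the only stratification factor. The Abstract gives the size: "Eighty children aged between 2 and 12 years old", hence 40 per arm.

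The Analysis section then says: "We will compare the two study arms groups using two-by-two chi-square tests for equality of proportions". The outcomes so compared are detected disease and adverse outcomes, with the imaging arm set against the slit lamp arm. The section names no stratified or adjusted comparison. In that section age appears only as a characteristic against which missing data will be explored. The same section also promises: "Proportions will be reported as point estimates with 95% confidence intervals". It says that effect sizes and variability will be given with 95% intervals to inform the full trial, but names neither a between-arm effect measure nor an interval method.

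The between-arm comparison is secondary. Study design makes feasibility metrics primary, and the primary clinical outcome under Study outcome measures is agreement between the two examinations within the imaging arm. Sample size adds that "there is no formal power calculation based on clinical non-inferiority for a diagnostic intervention".

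**The concern.** Blocking within age groups balances the arms on age, so variation in outcome between the age groups no longer contributes to chance differences between the arms. A test on one collapsed table still counts that variation as noise. If age predicts the outcome, the standard error is then too large and the true type I error falls below its nominal level.

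The sponsor chose age as the stratifier, and Table 1 sets length of surveillance partly by age at onset, with one band boundary between 8 and 9 years. It is therefore reasonable to allow for age predicting the outcome. At stake is how well an interval meant to inform a larger trial is calibrated.

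The Pearson chi-square also depends on adequate expected counts, which 80 children may not supply if uveitis is uncommon.

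**Working it through.** **Inputs from the article.** N = 80, 1:1, so 40 per arm; two age strata; unstratified two-by-two chi-square. A two-sided 5% level is inferred from the 95% intervals. There is no power figure to reproduce.

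**Assumed inputs.** The article gives no stratum sizes or stratum rates. I take 60% aged 8 or under (24 and 16 per arm), detection of 25% v 5% and 30% v 5% (younger v older), and 10% in both strata for the sparse case. All 80 children are analysed.

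**Step 1: standard error.** Pooled variance is p(1 − p), with p the overall rate. Within-stratum variance is the sum of w_k p_k(1 − p_k). The SE ratio is the square root of pooled over within.

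| Rates | Overall p | Pooled | Within | SE ratio |
|---|---|---|---|---|
| 25% / 5% | 0.6×0.25 + 0.4×0.05 = 0.17 | 0.17×0.83 = 0.1411 | 0.6×0.1875 + 0.4×0.0475 = 0.1315 | 1.036 |
| 30% / 5% | 0.6×0.30 + 0.4×0.05 = 0.20 | 0.20×0.80 = 0.1600 | 0.6×0.2100 + 0.4×0.0475 = 0.1450 | 1.050 |
| 10% / 10% | 0.10 | 0.0900 | 0.0900 | 1.000 |

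The 95% half-width for the difference is 1.96 × √(2 × variance / 40). At 25%/5% it is 16.5 percentage points unstratified and 15.9 stratified; at 30%/5%, 17.5 and 16.7.

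**Step 2: type I error.** Exact enumeration of all outcomes at 24 + 16 per arm, no true difference, Pearson test without continuity correction:

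| Rates | Planned chi-square | Cochran-Mantel-Haenszel | Exact stratified test |
|---|---|---|---|
| 25% / 5% | 4.4% | 4.9% | 2.5% |
| 30% / 5% | 4.1% | 5.0% | 2.6% |
| 10% / 10% | 5.9% | 5.1% | 1.7% |

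The direction reverses in the last row. With age not prognostic, the excess comes from sparse cells, not from ignoring the strata. An expected count falls below 5 when the two arms together have fewer than 10 events, which at a 10% rate has probability 0.72.

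**Step 3: point estimate.** The Mantel-Haenszel weight for a stratum is n1 × n0 / N. That gives 24×24/48 = 12 and 16×16/32 = 8, or 0.6 and 0.4 after scaling. These are the stratum shares, so the stratified risk difference equals the crude one exactly. Blocks of four keep the strata near this balance.

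**Step 4: wider range.** With per-arm splits of 20/20, 28/12 and 30/10 and rates from 10%/10% to 40%/10%, type I error runs from 3.7% to 5.9% for the chi-square and from 4.9% to 5.4% for Cochran-Mantel-Haenszel. The two tests disagree in about 0.1% to 1.3% of null trials. At an assumed common odds ratio of 4 (20/20 and 28/12 splits), stratifying adds about 1 to 5 points of power: from 61.2% to 62.7% at 15%/5%, and from 72.0% to 76.8% at 40%/10%, both with the 20/20 split.

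**The case against.** The strongest reply is that nothing in the article shows age to be prognostic for the tested outcome. Table 1 concerns how long surveillance lasts, by age at onset and subtype, not incidence within a year. Inside the trial, the visit schedule follows time since diagnosis, as the Fig 1 legend shows: "Visits for those entering study outside the 6-month widow: Day 1, Week 13, Week 26, Week 39, Week 52". If age does not matter, no precision is lost. This stands, and it is why every figure above is conditional.

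A second reply is that no decision rests on the test. The progression criteria are recruitment, adherence and sight-threatening complications in the imaging arm. This also stands and keeps the point minor.

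A third is that a statistical analysis plan, which the Dissemination section mentions, may add a stratified analysis. It may, but the article itself fixes the unstratified test, so the mismatch is on the page.

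A reader might infer two further things that the article does not support. One is that the full trial would receive a different estimate from the one a stratified analysis gives; Step 3 shows that the estimates essentially coincide. The Discussion also leaves open a different design in which each child has both examinations. The other is that the plan offers only a P value; the Analysis section does promise estimates with 95% intervals.

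**Conclusion.** The point holds as a minor mismatch between design and analysis. Under an assumed 60:40 split and 25% to 30% v 5% detection, an unstratified interval would be about 4% to 5% too wide and the type I error about 4.1% to 4.4%. Because the article names no interval method for the difference, the statement about width applies only if that interval is left unstratified.

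It would be wrong to conclude that the planned test is always conservative: at 10% in both strata it is slightly liberal, at about 5.9%. Nor does omitting the strata bias the comparison. The estimated difference is essentially unchanged, and neither a primary outcome nor a progression criterion depends on this test.

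**What to change.** In the Analysis section, replace the two-by-two chi-square with a between-arm risk difference stratified by the two randomisation age groups (Mantel-Haenszel), with its 95% confidence interval. If a P value is kept, use the ordinary Cochran-Mantel-Haenszel test. Do not require an exact version: its type I error was only 1.7% to 2.6% in the scenarios checked, further below 5% than the planned test in any of them, whereas the ordinary version stayed near 5%.

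The cost is one sentence, with no new data and no change to the sample size. The gain is modest, but the analysis then matches the randomisation and the between-arm effect measure is named.

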We aim to begin to provide the necessary high-level evidence, through a feasibility randomised controlled trial of AS-OCT versus routine clinical examination for the detection of uveitis in children at risk. This proof-of-concept study will compare imaging-based surveillance to the current approach of clinical examination (slit lamp examination-based surveillance) in the detection of uveitis in children with juvenile idiopathic arthritis The proposed study will provide the data needed to develop eligibility criteria, recruitment and retention approaches, to determine the key outcome metrics and study sample size necessary to demonstrate non-inferiority, and to inform the selection of the resource use measures needed to determine cost-effectiveness.

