**Fig 2 pone.0316410.g002:**
[figure not shown]
Details about the specific procedures during the intervention and control arm. * - See supplemental document 2 (S2) for specific visual acuity screening protocol.

Exit from the study will occur either at visit 7 (for participants with a new diagnosis of JIA within 6 months of entrance to study), at visit 6 (for participants whose JIA was diagnosed within 6 to 12 months of study entrance, Fig 1), or at any visit where uveitis has been diagnosed. A diagnosis of uveitis will be made clinically, using slit lamp examination. Any child within the intervention arm in whom a ‘disease positive’ AS-OCT is acquired (i.e., more than 1 hyper-reflective particle in any cross-sectional scan) will undergo a confirmatory slit lamp examination. Confirmation of uveitis will lead to a child exiting the study.

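### The between-arm chi-square test of 12-month detection says almost nothing about whether AS-OCT misses uveitis, and non-rejection of equality would not support non-inferiority

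*Protocol article*

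**What the plan says.** The between-arm analysis, in the Analysis section, consists of "two-by-two chi-square tests for equality of proportions for disease detection/ adverse outcomes within the OCT arm as compared with the" slit lamp group. No margin is given. The same section counts outcomes missing through attrition as adverse.

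Four other statements determine what this test can show:

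- Abstract: "Children in the intervention arm will also have standard examination at 6 and 12 months after study entrance".
- Abstract, clinical metric: "proportion diagnosed with uveitis or other ocular disorders at 12 months after study entrance".
- Text after the Fig 2 legend: "A diagnosis of uveitis will be made clinically, using slit lamp examination". An imaging-arm child with a positive scan "will undergo a confirmatory slit lamp examination".
- Sample size: slit lamp findings are assumed abnormal in 100% of children with active anterior uveitis. The non-inferiority concept is expressed as AS-OCT/slit lamp concordance of at least 95%, and a formal power calculation is disclaimed.

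The Introduction says the study will supply data for the "study sample size necessary to demonstrate non-inferiority" in a later trial. Study outcome measures names agreement of AS-OCT with clinical examination within the imaging arm, at 6 and 12 months, as the primary clinical outcome.

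**The concern.** A between-arm comparison of detection is informative about AS-OCT only if a case that imaging misses lowers the imaging arm's count. Here the slit lamp is both the reference test at 6 and 12 months and the means by which any diagnosis is made, and the outcome is read at 12 months, when the imaging arm has its last slit lamp. A missed case that lasts is therefore rescued into the detected column, and the comparison is pulled towards no difference.

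The hypothesis is a second problem. The programme's question is non-inferiority, but the test is of equality without a margin. Failing to reject equality in a small sample is not evidence of non-inferiority.

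Thirdly, detection and adverse outcomes are named together in one comparison, and attrition counts as adverse. Detecting disease is what surveillance is for, while an adverse outcome is a failure. If the two are pooled, the direction of an arm difference has no clear meaning.

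At stake is a between-arm result that looks reassuring by construction, for a potentially blinding disease, and that could be carried into the design of the full trial.

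**Working it through.** **Inputs from the protocol.** Total 80: "Eighty children aged between 2 and 12 years old and diagnosed with JIA within the preceding year will be included" (Abstract). Allocation: "1:1, block size = 4) stratified by age (8 and under, over 8" (Randomisation and allocation), hence about 40 per arm. Visits at months 2, 4, 6, 9 and 12 after the first visit (Study intervention). Slit lamp in the imaging arm at 6 and 12 months (Abstract). Slit lamp sensitivity 100% (Sample size).

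**Assumptions, because the protocol gives no figures.** Twelve-month uveitis incidence I of 5% to 30%; per-visit AS-OCT sensitivity s of 0, 0.5 or 0.8; onset uniform over the year; disease persists once present; all visits attended; two-sided 5% level. The protocol derives no power for its 80 children, so there is no stated figure to reproduce.

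**Step 1: expected detection with the 6- and 12-month slit lamps.** Onset in months 0–6 is found by the month-6 slit lamp at the latest, and onset in months 6–12 by the month-12 slit lamp. Detection by 12 months is therefore I × 1 = I in the imaging arm, for every s including 0. In the control arm it is also I. At I = 15% that is 0.15 × 40 = 6 expected cases per arm; at I = 20% it is 8 per arm. The exact rejection rate of the uncorrected chi-square test is then 4–6% across incidences of 5–30%, which is its type I error.

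**Step 2: where the misses go.** They appear only as delay. At s = 0, onset in the intervals ending at months 2, 4, 6, 9 and 12 is delayed by 4, 2, 0, 3 and 0 months, with weights 2/12, 2/12, 2/12, 3/12 and 3/12. The mean is (8 + 4 + 0 + 9 + 0)/12 = 1.75 months. At s = 0.5 it is about 0.8 months and at s = 0.8 about 0.3. A 12-month proportion does not measure delay.

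**Step 3: the same test without those slit lamps.** At I = 20% and s = 0, detection would be 0% against 20%, with power about 97%. At s = 0.5 with independent chances at each visit, it would be 20% × (2×0.96875 + 2×0.9375 + 2×0.875 + 3×0.75 + 3×0.5)/12 = 20% × 0.776 = 15.5% against 20%, with power about 8%. So the scheduled slit lamps hide a complete failure of imaging, but a moderate loss of sensitivity would be hard to see in any case.

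**Step 4: what non-rejection is worth at 40 per arm.** The table gives power by exact binomial enumeration if half the cases were missed at every visit and not rescued, and the 95% CI half-width for the difference when both arms have rate I: 1.96 × √(2 × I × (1 − I)/40).

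| Assumed I | Expected cases per arm | Power to see detection halved | CI half-width (points) |
|---|---|---|---|
| 10% | 4 | 0.146 | 13.1 |
| 15% | 6 | 0.198 | 15.6 |
| 20% | 8 | 0.247 | 17.5 |
| 30% | 12 | 0.366 | 20.1 |

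At I = 15%: 1.96 × √(2 × 0.15 × 0.85/40) = 1.96 × 0.0798 = 0.156.

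**Step 5: scale of a non-inferiority comparison.** With equal true rates, one-sided 2.5% and 80% power, an assumed 10-point margin needs 142, 201, 252 and 330 per arm at incidences of 10%, 15%, 20% and 30%. This is context only; the protocol does not claim such power.

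**Step 6: the analysis that can show misses.** In the paired agreement each imaging-arm child has both tests at 6 and 12 months, so a negative scan with a positive slit lamp is visible as a discordant pair. As an example of its precision, 38 of 40 concordant (95%) has a Clopper–Pearson 95% CI of 83.1% to 99.4%.

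**The case against.** The strongest reply is that the design already handles the question. The 6- and 12-month slit lamps are there to serve as the reference test for the paired agreement, which is the primary clinical outcome. The main outcomes are feasibility metrics. Progression rests on recruitment, sight-threatening complications and adherence, not on a p-value for detection. The protocol disclaims non-inferiority power and leaves that demonstration to the full trial, and it already promises proportions with 95% confidence intervals. All of this stands, and it limits the weight of the point. It does not make the between-arm test informative: the Analysis section still prescribes it without a caveat, and the limitations in the Discussion do not mention the issue.

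A reader might infer more than the protocol supports:

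- *That the trial cannot show AS-OCT misses.* It can, through the paired agreement.
- *That a non-significant test will be presented as non-inferiority.* No sentence says so; the concept is tied to 95% concordance.
- *That the estimates passed to the full trial would be invalid.* The Analysis section refers to effect sizes for discrimination of disease, which reads most naturally as the paired data, and the control-arm proportion is unaffected.
- *That equality of the arms is certain.* It is exact only for disease that lasts to the next slit lamp in a child who attends. Disease that resolves earlier, or a reading of detection as scan-triggered only, could leave a difference. The slit lamp definition of diagnosis makes that last reading less likely but does not exclude it.

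Low power on its own is no error in a feasibility trial.

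**Conclusion.** The point holds for the secondary between-arm test. For persistent disease in children who attend, and with slit lamp sensitivity at the protocol's assumed 100%, 12-month detection has the same expectation in both arms at any AS-OCT sensitivity, so the test rejects at about its type I error rate. Non-rejection could not support non-inferiority even without this masking: at an assumed 15% incidence, power to see detection halved is about 20% and the 95% CI half-width about 16 points, and the conclusion is the same from 10% to 30%. Incidence and AS-OCT sensitivity are assumptions throughout; the equality in Step 1 depends on neither. The feasibility outcomes, the primary clinical outcome and the progression criteria are unaffected. Should-fix, not a threat to the trial.

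**What to change.** In the Analysis section:

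1. Replace the equality test with a risk difference and 95% CI, labelled descriptive, with no claim of significance or non-inferiority. Stratifying by the randomisation age groups is optional; with about six events per arm it would add little.
2. In the imaging arm, report each diagnosis as AS-OCT-triggered or as found only at the scheduled 6- or 12-month slit lamp, and count the latter as AS-OCT misses.
3. Analyse disease detection separately from adverse outcomes, so that attrition counted as adverse is not pooled with detection.
4. State that inference about missed disease, and the discrimination estimates for the full trial, rest on the paired within-arm agreement.

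The cost is a change of wording and a small extra table. How each case was found should follow from the visit data; no visit, examination or recruitment target changes.
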